## Background

People with highly-functioning social networks are better able to give and receive support, are more psychologically resilient, and live longer and healthier lives [1]. Regrettably, various reports and signals from the field suggest that the current professional approach fails to provide frail elderly people with needed social support networks to make living conditions safer, more stimulating, comfortable, and pleasant and to enable them to live in their own neighbourhoods for a longer time. Strengthening social networks fosters early detection of problems, is crucial to public health, and is expected to reduce the pressure on the healthcare system by preventing or delaying nursing home admissions. Facilitating elderly people through an Integrated Neighbourhood Approach (INA) to live independently for as long as possible requires a supportive community environment, which is in turn dependent on the presence of meeting places [2], mutual interdependence of residents, and motivation to invest in local relationships reflected, for example, by residential stability [3]. Neighbourhood differences in this regard have been reported. An important condition seems to be that the community engage in shared activities, thus establishing contacts through which social networks can develop [4,5]. Residents will be more inclined to participate in neighbourhood activities if they perceive a sense of community [6]. Currently, the frail elderly have to depend on professional care; informal networks and social support are underemployed [7].

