#### Evaluation design

Our evaluation study uses a concurrent mixed-methods design (a combination of qualitative and quantitative research methods) to evaluate processes, effects and costs of INA. A frequent shortcoming of evaluation studies is failure to give good descriptions of what was done and the context in which it was done [11]. In the first phase (months 1-6), therefore, the eventual local-level interventions will be described extensively along with how welfare, care, and network support for frail elderly persons and their informal caregivers is achieved. A good description of interventions is the first step and towards that, key figures including community workers will be interviewed.

The evaluation will comprise (I) inventory and (II) controlled pre-post measurement. Inventory is taken among the elderly (70+) in the four relevant districts (Lage Land/Prinsenland, Lombardijen, Oude Westen, and Vreewijk) to investigate the general situation of elderly in these districts. Furthermore, we investigate social networks, social cohesion, and the sense of community in these districts to learn if INA contributed not only to elderly included in the experiment, but to the wider context as well.

The controlled pre-post measurement is the main part of the evaluation. Independently-living elderly (70+) in the first two districts will serve as the experimental group (Figure 1).

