#### Sample size

We will include 370 elderly (2/3 in intervention group, 1/3 in control group). We will try to limit sample losses by personal house visits, but expect a loss of about 27% (by death, moving, no longer wishing to participate, etc.) between T0 and T2, resulting in a final sample of 270. This number - 180 in the intervention group and 90 in the control group - is required to detect a 1-point improvement in TFI-score in the intervention group as compared with the control group at T2 (with mean TFI-score 4.7, sd 3.0; one-sided test; alpha = 0.05, power = 0.80) [12].

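### The stated 80% power treats 270 people as independent although INA is allocated by district; it holds only if the district ICC is close to zero or baseline adjustment gains precision, and should be restated as conditional

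*Protocol article*

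**What the plan says.** The Sample size section gives every input of a two-group comparison of means: "with mean TFI-score 4.7, sd 3.0", a 1-point difference at T2, and "one-sided test; alpha = 0.05, power = 0.80". The 180 + 90 people expected to complete T2 are presented as the number that "is required to detect a 1-point improvement in TFI-score in the intervention group as compared with the control group at T2". Allowing for an expected loss of about 27%, recruitment is 370 (247 + 123). No ICC, design effect or number of districts enters.

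Under Evaluation design, elderly people "in the first two districts will serve as the experimental group". The section on the controlled pre-post measurement narrows this to those with TFI ≥ 5 recruited by community workers. It takes the controls from other, comparable Rotterdam districts, matched on TFI-score, age and gender. The number of control districts is not stated. The Setting section describes INA as working through neighbourhood networks. The Background says of the conditions for a supportive community: "Neighbourhood differences in this regard have been reported".

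**The concern.** Arm and district coincide: no district contributes people to both groups. If people in one district resemble each other on the TFI for reasons unrelated to INA, 90 people from one district carry less information than 90 independent people. The standard error behind the 0.80 is then too small. The intervention acts on neighbourhood networks and the TFI has a social domain (Instruments elderly, Frailty), so some district correlation is plausible.

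At stake is whether a null result could be read as evidence against INA and, depending on the model used, whether an ordinary district difference could be declared significant. The effect result also feeds a cost-utility analysis meant to inform local and national decisions.

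**Working it through.** **1. The plan's own figure.** Inputs from the Sample size section: difference 1, SD 3.0, one-sided alpha 0.05 (z = 1.645), power 0.80 (z = 0.842), ratio 2:1.

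- Control n = (1.645 + 0.842)² × 3.0² × (1 + 1/2) / 1² = 83.5, so 84. Total 84 + 168 = 252.
- At 180 + 90: SE = 3.0 × √(1/180 + 1/90) = 0.387. Power = Φ(1/0.387 − 1.645) = 0.826.
- Dropout: 270 / 0.73 = 370, as stated.

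The 270 is not reproduced exactly, but it lies on the safe side of an independent-observations calculation. The slack is 270 / 252 = 1.07. A two-sided test would need 318, so it does not explain 270.

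**2. Allowing for districts.** Assumptions: 90 completers in each experimental district (even split); k control districts of 90/k each; ICC = ρ.

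SE² = SD² × { [1 + 89ρ]/180 + [1 + (90/k − 1)ρ]/90 }

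Power (normal) = Φ(1/SE − 1.645). For a district-level test, power comes from a noncentral t with 2 + k − 2 = k degrees of freedom.

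**3. The ICC at which 80% is lost.** Power of 0.80 needs SE ≤ 1/(1.645 + 0.842) = 0.402, so SE² ≤ 0.1617. For k = 2 the formula becomes SE² = SD² × (0.01667 + 0.9833ρ).

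- SD 3.0: 0.1617/9 = 0.01797, so ρ ≤ (0.01797 − 0.01667)/0.9833 = 0.0013. With 4 or 10 control districts the limit is 0.0018 or 0.0022.
- Residual SD 2.4 (assumed): 0.1617/5.76 = 0.02807, so ρ ≤ 0.0116.

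**4. Power and test size, two control districts.** SD 2.4 equals 3.0 × √(1 − 0.6²), which assumes a T0–T2 correlation of 0.6 and the same ICC in the residuals.

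| ICC | SE (SD 3.0) | Power, normal | Power, 2 df | Power, normal, SD 2.4 | Power, 2 df, SD 2.4 | Size of individual-level 5% test |
|---|---|---|---|---|---|---|
| 0.001 | 0.399 | 0.81 | 0.51 | 0.93 | 0.65 | 0.055 |
| 0.01 | 0.488 | 0.66 | 0.40 | 0.82 | 0.52 | 0.096 |
| 0.02 | 0.572 | 0.54 | 0.33 | 0.71 | 0.43 | 0.133 |
| 0.05 | 0.770 | 0.37 | 0.23 | 0.49 | 0.30 | 0.204 |

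The last column is 1 − Φ(1.645 × 0.387/SE). SD cancels, so at a given ICC baseline adjustment does not improve it.

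**5. More control districts, SD 3.0.** At ICC 0.01, normal power is 0.69 with four and 0.72 with ten (0.55 on 4 df, 0.66 on 10 df). At ICC 0.02 it is 0.59 and 0.63. This helps only partly, because the two experimental districts dominate the variance.

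**6. More people per district.** With 2 + 2 districts and unlimited people at ICC 0.02, SE² tends to 9 × 0.02 × (1/2 + 1/2) = 0.18. Power on 2 df is then only about 0.47.

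**The case against.** A reader might infer that the design certainly has less than 80% power. The documents do not support that. They give neither an ICC nor the number of control districts, and under the normal approximation power is still 0.81 at ICC 0.001. Subjects are matched on baseline TFI and measured at T0, T1 and T2, and Data analysis foresees longitudinal multivariate work. A baseline-adjusted model could therefore hold about 0.82 at ICC 0.01. SD 3.0 is quoted with a mean of 4.7, below the entry cut-off of 5, so the enrolled group may have another SD; an assumed 2.5 without adjustment gives 0.79 / 0.68 / 0.47 at ICC 0.01 / 0.02 / 0.05. All of this stands and is why the loss is shown as a range.

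A reader might also infer that the planned test is too liberal. The article names a one-sided test for sizing only and does not name its final model. The handling of clustering may be set out in an analysis plan that is not shown. The 10–20% size figures therefore apply only if the final analysis is individual-level with no district term.

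The Background remark on neighbourhood differences concerns meeting places, mutual interdependence and residential stability. It makes a district effect plausible but says nothing about the size of a TFI ICC. Part of INA is also individual, through home visits and needs interviews.

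Lastly, the article concedes that it cannot randomise and relies on matching. That concedes confounding but does not address the power figure: matching on TFI-score, age and gender cannot separate a district effect from the INA effect. None of these objections makes the unconditional 0.80 follow from the stated design.

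**Conclusion.** The concern holds in a conditional form. The stated power comes from independent observations, while allocation is by district with only two experimental districts. The 270 absorbs a design effect of about 1.07, so at SD 3.0 and under the normal approximation 80% requires a district ICC of about 0.001–0.002 or less. Over ICC 0.01–0.05 with two control districts, power runs from 0.66 to 0.37 unadjusted and from 0.82 to 0.49 with an assumed residual SD of 2.4. On 2 degrees of freedom it is below 0.80 throughout, even at ICC 0 (0.52 at SD 3.0). These ranges rest on assumed ICC, residual SD, even split and number of control districts. Inflated test size is a further risk, conditional on the final model.

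**What to change.** - Replace the unconditional 0.80 with a small table of power over ICC 0.001–0.05 and over the number of control districts, with and without baseline adjustment, and state the assumed residual SD.
- Report the INA effect with a sensitivity analysis that either inflates its standard error over that ICC range or uses district-level small-sample degrees of freedom. Do not rely on cluster-robust errors: with so few districts they are themselves unreliable. Two experimental districts also give little basis for estimating a district variance from the data.
- Draw the same 123 controls from several comparable districts where feasible, and state how many.
- Word the conclusion as applying to the districts studied, because arm and district are confounded.

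The cost is a less favourable stated power, a wider interval and some extra fieldwork travel. No extra participants are needed; the working shows that recruiting more people in the same districts would not solve the problem.

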##### Ethical approval

The study protocol was approved by the ethics committee **of the Erasmus University Medical Centre of Rotterdam in June 2011. R**espondents will receive a brochure prior to the interview to explain the study and procedure, provide a free helpdesk telephone number, and state that the Medical Ethical Review Board of Erasmus MC has issued a Certificate of No Objection after having established that the study complies with the Dutch Act on Medical Research in Humans. The respondents' informal caregivers will also receive a brochure with information about the study and an invitation to participate. Both the elderly and their informal caregivers will be explicitly informed in the brochure and by the interviewer that participation can end at any time without adverse consequences. Written informed consent will be obtained from all participating respondents.

### Evaluation components

The evaluation study has three parts: (i) process (ii) effects, and (iii) costs of INA (Figure 2).

**Figure 2 F2:**
[figure not shown]
**Process and effect evaluations; cost-effectiveness evaluation**.

#### i. Process

The process evaluation study will find whether INA contributes to (a) continuous, demand-driven, coordinated care and support for independently-living frail elderly, and (b) reinforcing the welfare, health care, informal care and community networks in their neighbourhoods. We will describe INA in Rotterdam, how the various networks are reinforced, what they do, and how they cooperate to improve the self-management abilities and well-being of frail elderly. Process indicators will be registered continually during 12 months. Data such as descriptions of client visits, assessment outcomes, action goals, and agreements will be captured by a computerized Client Monitoring System and registration forms. An evaluation of the process indicators and data about contacts with professionals is expected to reveal any INA effects.

We will hold semi-structured interviews with professionals, key figures, neighbours, elderly and their caregivers to provide insight into possible barriers and conditions under which proposed changes take place. Earlier research has shown, for example, that conflicting priorities, lack of specificity of and consensus on intended changes, and professionals' insufficient commitment can be important barriers [13]. We will also investigate the experiences of professionals and key figures via questionnaires. Since the effectiveness of a transition experiment is strongly dependent on the implementation process, we would like to know what conditions promote or limit the effectiveness of welfare and care support in neighbourhoods to get an even better understanding of the success of the intervention(s) and the merit of INA for other settings [11]. All professionals (community workers, district nurses) and key figures directly involved in the care and support of the elderly will be given a written questionnaire at T0 and T1. The instrument is partly based on the partnership self-assessment tool [14], which is currently being tested in a disease management study [15] and validated via interviews in its first phase. Aspects addressed in the questionnaire are (a) participation of the professionals and key figures involved in INA (partnership synergy); (b) different dimensions of partnership functioning (leadership, control and management, efficiency, non-financial resources, challenges in partners' commitment and to the municipality/district); and (c) relational coordination (frequency of communication between parties involved, quality of the communication, extent of shared goals, knowledge, and respect) [16] (table 1).

**Table 1 T1:** Outcome and process instruments

Primary outcomes elderly	Instruments	Items

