The point of departure of INA is reinforcing networks between welfare, health care, informal care and community members in neighbourhoods, optimizing current services, and involving the (frail) elderly. Such a demand-driven approach offers elderly people tailored care - including care-related services such as housing - in their local context to enhance self-management abilities and well-being. The focus is on "de-medicalisation" and recognition of mutual dependence between welfare, health care, and informal care. Thus, for INA to be successful the partners in primary, secondary, and tertiary care as well as informal networks need to work well together - from signalling problems to prevention, cure, care, promotion of welfare, and independent living. Early recognition of complaints and encouraging effective self-management may positively influence well-being. It requires the elderly to 'star' in the 'production' of their own well-being as a form of empowerment [8]. Informal caregivers play a central role in their social networks and are important to supporting independent living. Evidence suggests that caring for a frail elderly person is an arduous task that may cause financial difficulties, emotional strain, or physical problems [9,10]. A supportive network for elderly may alleviate such negative aspects of caregiving, which in turn helps sustain informal caregivers' support.

While INA may improve outcomes, evidence regarding the (cost-) effectiveness of such programmes is lacking. The purpose of our research is to investigate how an INA can contribute to outcomes of the frail elderly and its cost-effectiveness. The first central study question is: To what extent does INA contribute to (a) continuous, demand-driven, coordinated care and support for the independently- living frail elderly and the well-being of their informal caregivers; (b) improvement of their well-being and self-management abilities; and (c) reinforcement of their neighbourhood networks. The second central research question is: is the INA a cost-effective method to support the frail, independently- living elderly?

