#### Setting: Dutch example of an Integrated Network Approach

Although welfare and health care are widely available in the city of Rotterdam, the specific needs of frail elderly remain inadequately addressed and 'outreach' work is lacking. A number of 'best practices' may exist locally, but not a good overview of the services because of fragmentation and compartmentalisation. Such services are difficult for the elderly to find and are not visible to others in the city. In the current situation the frail elderly have to depend on professional care, while informal networks and social support are underused. An INA is based on reinforcing neighbourhood networks through which continuous, demand-driven, coordinated care and support can eventually be offered to all independently-living frail elderly persons. Community workers - professionals with a care or welfare background familiar with the residential area - are important to the network. They visit the elderly at home and map their wishes and needs via a phased interview. In consultation with the elderly, they seek appropriate solutions within the (preferably informal) network. Such a transition experiment aims to facilitate independently-living frail elderly persons (70+) to live the life they wish to live, improving their well-being. The study population consists of independently-living frail elderly persons and their informal caregivers in Rotterdam. The transition experiment begins in two Rotterdam districts (*Lage Land/Prinsenland *and *Lombardijen) *and is later extended to the *Oude Westen *and *Vreewijk *districts.

The project ('An integrated neighbourhood approach to welfare and care for the frail elderly in Rotterdam') and the associated evaluation study are part of the National Care for the Elderly Programme (NPO) launched in the Netherlands in 2008. Funding is provided by the Netherlands Organisation for Health Research and Development (ZonMw; project number 314030201).

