#### iii. Costs

A cost-effectiveness evaluation will be performed to determine whether INA is a cost-effective method to support the frail, independently-living elderly. We will assess the additional (health care) costs involved in INA and the costs per quality-adjusted life years (QALY) gained in the elderly and their informal caregivers. INA costs may be higher than expected because extra care and support are offered and more people could avail themselves of the services, or they may be lower than expected because specific groups of elderly and their informal caregivers will earlier and more purposefully avail themselves of the services and receive better support from their networks, preventing or delaying serious (health) problems. Delaying or preventing admission to a nursing home, for example, lowers costs and often appeals to the elderly and informal caregivers.

Health care utilization and given support will be quantified via questionnaires and additional sources where possible (Client Monitoring System, local and national monitors). Multiplying these volumes by integral cost prices will yield total costs of care and support. For this purpose we will use the guideline of the Dutch Health Care Insurance Board (CVZ) [38]. INA costs are estimated via time registrations on professionals' activity levels. Different types of activity (such as contact with the elderly and team meetings), professional disciplines, and corresponding tariffs will be taken into account. Assessment costs will be included in the total costs for the intervention group only and not the control group, because the costs are incurred only within the INA framework. Finally, costs per centre will be calculated (e.g., costs of the interventions, welfare, health care, community workers), providing insight for all participating organizations as to the investments that will be needed to continue INA after the study phase.

The cost-effectiveness evaluation will be on the basis of the costs and the registered effects described above. The primary analysis is a regular cost-utility analysis with differences between the intervention and control groups in costs and well-being (QALY) during a 12-month follow-up as outcome, allowing us to compare findings with other studies.

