### Data analysis

Data on defined outcome measures for the process- and (cost-)effectiveness evaluations will be collected at T0, T1, and T2 for the elderly and at T0 and T2 for the informal caregivers. They will be described and analysed as follows:

- Descriptive statistics at the group and district levels at different time points;

- Bivariate analyses relating outcome measures to the elderly's socio-demographic characteristics and process indicators;

- Correlation analysis between various types of outcomes;

- Multivariate analysis of outcome measures per time point and longitudinally;

- Subgroup analyses to determine whether outcomes strongly vary for different groups (e.g., single vs. partnered, low vs. high self-management abilities);

- Sensitivity analyses to determine the influence of major assumptions on reported outcomes.

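### INA delivery records cannot by themselves reveal an effect of INA, and relating process indicators to outcomes bivariately is open to confounding by need

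*Protocol article*

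**What the plan says.** All references are to the Protocol article.

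- **i. Process.** The data registered over 12 months are delivery records: "descriptions of client visits, assessment outcomes, action goals, and agreements will be captured by a computerized Client Monitoring System", together with registration forms. The section then says: "An evaluation of the process indicators and data about contacts with professionals is expected to reveal any INA effects".
- **Data analysis.** One of the six listed steps names process indicators: "Bivariate analyses relating outcome measures to the elderly's socio-demographic characteristics and process indicators". A separate step reads "Multivariate analysis of outcome measures per time point and longitudinally" and names neither covariates nor process terms.
- **Background.** The service has no fixed intensity: "Such a demand-driven approach offers elderly people tailored care".
- **Setting.** Community workers begin from need: "They visit the elderly at home and map their wishes and needs via a phased interview". Solutions are then sought, preferably in the informal network.
- **iii. Costs.** "Assessment costs will be included in the total costs for the intervention group only and not the control group", because those costs arise only within INA.
- **Evaluation design, Controlled pre-post measurement and Sample size.** The main part of the evaluation is the matched comparison of INA with control, and the sample size is based on the difference in TFI at T2.

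**The concern.** When a service is tailored to the person, the amount delivered is partly a marker of need. Need at T0 also predicts frailty, quality of life and cost at T2, whether or not INA works. Within the INA group, more visits or more agreed actions may therefore go with worse T2 scores even if INA does nothing. If INA helps, the same mechanism can hide or reverse the benefit.

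Two features of the text invite this error. The Process section says the records are expected to reveal effects, which is an inferential claim and not a descriptive one. The one listed analysis that links process indicators to outcomes is bivariate, and a bivariate analysis makes no allowance for need.

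At stake is the interpretation of the process data: whether INA contributed, and whether more of it was better or worse. The main effect estimate is not at stake.

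**Working it through.** The plan gives no figure on this point, so the check has two parts: reading the sections together, and illustrating the mechanism under stated assumptions.

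**1. Reading the sections together**

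- *Are the data delivery records?* Yes. Visits, assessments, goals and agreements are things INA does.
- *Is there a control counterpart?* None is stated for the monitoring system. The Costs section places assessment costs in the intervention group only, which points the same way.
- *Does intensity follow need?* The Background and Setting sections make this likely. It is not certain, because solutions are preferably informal and greater need may not always mean more professional contact.
- *Does the listed analysis allow for need?* The bivariate step does not. The multivariate step might, but it does not mention process indicators.

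**2. Illustration with zero true effect**

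Inputs from the Sample size section: 180 INA completers, TFI SD 3.0, target difference 1 point. Assumed, not from the article: correlation a between contacts and T0 TFI of 0.2 to 0.4, and correlation b between T0 and T2 TFI of 0.5 to 0.7.

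If contacts relate to T2 TFI only through T0 TFI, then:

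- spurious r = a × b
- Fisher z statistic = atanh(r) × √(180 − 3), compared with 1.96 (two-sided 5%)
- apparent TFI points per SD of contacts = 3.0 × r

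| a | b | r | z | Share of studies significant | TFI points per SD |
|---|---|---|---|---|---|
| 0.2 | 0.5 | 0.10 | 1.33 | 27% | 0.30 |
| 0.3 | 0.6 | 0.18 | 2.42 | 68% | 0.54 |
| 0.4 | 0.7 | 0.28 | 3.83 | 97% | 0.84 |

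A higher TFI is worse, so the spurious association looks like harm.

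A separate simulation (2000 runs per setting, 180 people, no true effect) used wider assumptions: need-contact correlation 0.2 to 0.5 and need-TFI correlation 0.3 to 0.7. The bivariate slope was +0.18 to +1.05 points per SD of contacts, with p < 0.05 in 10% to nearly 100% of runs. After adjustment for need measured without error, the slope was about 0.

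**3. Sensitivity to the entry rule**

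Participants must score at least 5 on the TFI, while the SD of 3.0 goes with a mean of 4.7. Suppose the assumed correlations belong to that unselected population and TFI is roughly normal. Cutting at 4.5 (5 less half a point, as scores are whole numbers) reduces the T0 SD to about 1.84, a ratio u = 1.84/3.0 = 0.615. Each correlation c becomes c·u / √(1 − c² + c²u²).

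- Low case: 0.2 becomes 0.125 and 0.5 becomes 0.335, so r = 0.04.
- Central case: 0.3 becomes 0.190 and 0.6 becomes 0.419, so r = 0.08.
- High case: 0.4 becomes 0.259 and 0.7 becomes 0.516, so r = 0.13.

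The share significant falls to 9% to 43% (about 18% in the central case), and the apparent harm to about 0.1 to 0.3 points. The direction is unchanged.

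**The case against.** The strongest reply is that the article already separates process from effect. The controlled comparison is called the main part and is headed as the effect evaluation, the sample size rests on it, and the primary cost-utility analysis uses differences between the groups. The process part opens with its own questions, on coordinated care and reinforced networks, and delivery records are natural evidence there. The Data analysis section is a six-line outline in a condensed article, so unnamed covariates are no fault.

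Much of this stands, and it rules out several stronger readings that a reader might infer:

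- *That INA effects are to be revealed through the bivariate analyses.* The Process section names no method, and the Data analysis section does not refer back to it. The link is an inference from reading the two together.
- *That all contact data exist only for the INA group.* This fits the monitoring system. Care use and support are also collected by questionnaire, and the between-group cost comparison needs them in controls.
- *That the promise in the Abstract to show which elements are potentially (cost-)effective rests on this relation.* The Abstract credits the mixed-methods design as a whole.
- *That process indicators must mean contact counts.* Table 1 also lists partnership and coordination questionnaires, which professionals and key figures complete. However, the Process section gives the client records as its example of what is registered continually.
- *That the size of the bias is known.* It is set by the assumed correlations and by how the entry rule is treated.

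The objection does not remove the sentence itself. It speaks of any INA effects, without limiting them to coordination and networks. Even for those two questions, asking whether INA contributes is causal, and delivery records with no comparator do not answer it alone. Nor is the complaint that covariates are missing: the step the article does state is bivariate.

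**Conclusion.** The point holds in limited form. The sentence in the Process section claims more than needs-led delivery records without a stated control counterpart can support. The only listed analysis naming process indicators is open to confounding by indication. The likely direction is apparent harm or masked benefit.

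The magnitudes are illustrative only. They rest on assumed correlations, no true effect and, for the second range, normality and an unselected reference population: 0.3 to 0.8 TFI points per SD of contacts without range restriction and about 0.1 to 0.3 with it, against a target of 1 point.

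A reader should not conclude that the INA-versus-control estimates of effect or cost-utility are biased by this, because nothing in the article makes them depend on the process data. The correction is worth making because it is cheap and prevents a misleading reading of the process results.

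**What to change.** - **i. Process:** replace the sentence on revealing effects with a statement that effects of INA on outcomes are judged from the controlled comparison, and that process indicators and contact data describe delivery, reach and intensity.
- **Data analysis:** take process indicators out of the bivariate step. Analyse process-outcome associations within the INA group, adjusted for T0 values already collected: the T0 value of the outcome, TFI, Katz-15, SMAS-S, age and partner status. Label the results exploratory and non-causal.

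The cost is wording in two sections and one additional model, with no new data. The process data will support a weaker claim, and adjustment for measured need may leave residual confounding, which the report should acknowledge.
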